### Data collection

Our proposed primary and secondary outcome measures are outlined below. These were discussed and considered collaboratively with MST professionals, and further reviewed by participants who took part in our phase 1.2 interviews. Eligible participants complete outcome measures 4 weeks before the commencement of treatment, and then at up to 13 (mid-point), up to 26 (end of treatment), and 52 weeks (12-month–6-month follow-up) from treatment commencing.

### Screening measures

Participants and their families will initially be invited to take part in a screening interview to ensure that they meet the eligibility criteria for the study, including the collection of evidence to confirm that a child is at risk of exploitation. Children and teenagers will be invited to complete the Wechsler Abbreviated Scale of Intelligence-II [19]. Referrers (e.g., youth offending teams, child and adolescent mental health teams) will be asked to confirm the presence of antisocial behavior.

### Candidate primary outcome measure

The candidate primary outcome measure is the Self Report Delinquency Measure (SRDM) [20] which was developed and used as part of a longitudinal study of criminal offending behaviors amongst 4300 children in Edinburgh. This is a short measure comprising 15 items pertaining to antisocial behaviors (e.g., burglary, violence) which require children to respond with yes or no with reference to a time period, and then report the estimated frequency of behavior, and whether they have ever been caught. There is evidence that asking respondents to indicate whether they have engaged in these behaviors is accurate [21, 22], and this measure has been previously used as an outcome measure within a randomized controlled trial of MST [10].

### Secondary outcome measures

Potential secondary outcome measures include (1) crime data: we will work with sites to gain information about arrests, cautions, reprimands, warnings, and convictions for participants with consent from parents. We aim to initially collect crime data over the prior 6-month period to the commencement of treatment, during treatment, and during the 6-month follow-up period. (2) Empathy: we will use the parental/carer version of the Griffith Empathy Measure (GEM) [23] which is a short 23-item measure of cognitive and affective empathy for children and adolescents which can be used with children aged from 4 years. The GEM has robust psychometric properties [23]. (3) Callous and unemotional traits: this will be measured using the 24-item Inventory of Callous and Unemotional Traits–Parent Report and Youth Self-Report Versions [24] which are robust and well-validated instruments [25]. (4) Well-being: the parent and self-report version of the Strengths and Difficulties Questionnaire (SDQ) will be used to assess child and teenager well-being. The SDQ is a robust and well-validated measure of behavioral and emotional problems [26]. (5) Peer Deviance: The Behavior of Friends Questionnaire (BFQ) [27] is a short 10-item checklist that assesses peer delinquency by asking respondents to indicate whether their friends engage in a variety of antisocial behavior (e.g., lying, stealing) using a 5-point Likert scale. The measure has been shown to have excellent internal consistency [27]. (6) Parenting: the Alabama Parenting Questionnaire has robust psychometric properties and measures parental involvement, positive parenting, monitoring/supervision, inconsistent discipline, and punishment. Both the parent and child-completed versions will be used [28, 29]. (7) Satisfaction: at the end of treatment, we will assess acceptability by asking all children, adolescents, and parents to complete a short questionnaire containing 10 items that are answered using a Likert scale. Items specifically ask about satisfaction with taking part in the intervention. (8) Social deprivation: we will draw on data from the UK Indices of Multiple Deprivation to identify families living in deprived neighborhoods according to participants’ postcodes (i.e., zip codes). (9) Family functioning: Family Adaptability and Cohesion Scales–IV (FACES-IV) is a 62-item self-report measure that assesses cohesion, adaptability, communication, and satisfaction within a family system [30]. (10) Gang affiliation: the Gang Affiliation Risk Measure (GARM) [31, 32] is a short 15-item measure of gang affiliation that was developed with teenagers and young people from England.

#### Phase 2.2: process evaluation

Initially, we refined a logic model together with MST experts which will be used to directly inform our process evaluation. This will consider but is not limited to (i) the impact of additional staff training, (ii) how partnerships with stakeholders are strengthened, (iii) the processes that promote or hinder greater engagement with voluntary and community agencies and other positive activities, and (iv) the processes that increase or hinder engagement in education and school transition. We will develop a series of process indicators drawn from the logic model that we will measure throughout the study. We have also completed interviews with clinicians, stakeholders, families, and young people to refine MST tools for working with families where there is a risk of criminal exploitation, and to consider the most appropriate method of measuring outcomes from MST for children at risk of criminal exploitation. In addition, we will recruit families (*n* = 12) and clinicians and stakeholders (*n* = 12) to complete in-depth interviews as part of our process evaluation to further consider whether the augmentations to MST for children at risk of criminal exploitation were successfully implemented, with reference to our logic model, and any associated factors that facilitated or hindered the successful implementation. We will also attempt to interview families who have dropped out of treatment in order to understand the reasons (*n* = 6) as part of the 12 families that we intend to recruit.

### Analysis

As this is a feasibility study, the quantitative analysis will be descriptive in nature. Continuous data will be reported as means and standard deviations, or medians and interquartile ranges, as appropriate. Categorical data will be reported as frequencies and proportions. All data will be reported both overall and by site including recruitment and retention rates, outcome measure completion rates, and missing data rates. Outcomes will be estimated with their associated 95% confidence intervals. The study will be reported in accordance with the CONSORT extension for randomized pilot and feasibility studies [35].

Interviews will be transcribed and analyzed using Framework Analysis [14] which is well suited to this context because we have specific questions, an awareness of potential issues, and a pre-designed sample. This method allows researchers to investigate key issues of interest, rather than analyze data for emergent themes including the acceptability of the intervention and research procedures. We will triangulate data by comparing data collected during the focus groups, the feasibility study, and the interviews with families and clinicians, highlighting areas of agreement and disagreement using a triangulation protocol, integrating our qualitative and quantitative findings, similar to previously used methods [33, 34]. Data from all sources will be analyzed independently, and then compared using three different types of triangulation: (a) methodological—using more than one method to collect data, (b) data—using multiple data sources, and (c) investigator—using multiple researchers to analyze the data.

The outcomes that will be analyzed in order to judge the feasibility of completing a larger study are: (a) the acceptability and feasibility of MST-E for stakeholders, including families, including a description of factors that facilitate or hinder the implementation of the intervention, (b) the appropriateness of our measures in terms of their use within a future pilot trial including completion and missing data rates, (c) the appropriateness of an adapted fidelity checklist, if used, (d) the accrual and retention rate and willingness of teams to recruit participants, (e) therapy completion rate and attrition, and (f) the within-group effect size on our proposed primary and secondary outcome measures.

### Progression criteria

Green: (a) intervention acceptability: all stakeholders, including families judge the intervention and the associated changes from standard MST to be acceptable, (b) candidate outcome measures: 95% of recruited participants complete the outcome measures on all occasions and rates of missing data are below 5%, (c) fidelity checklist: an adapted fidelity checklist is judged to be acceptable by stakeholders with a completion rate of 95%, and (d) recruitment and retention: 100% of participants are recruited, the accrual rate is 2:1, and the retention rate is at least 80%.

Amber: (a) intervention acceptability: some stakeholders, including families raise concerns about the acceptability of the intervention, which may include confusion about how the intervention is sufficiently different from standard MST, (b) candidate outcome measures: fewer than 95% but more than 80% of recruited participants complete the outcome measures on all occasions and rates of missing data are more than 5% but less than 10%, (c) fidelity checklist: an adapted fidelity checklist is judged to be acceptable by stakeholders with a completion rate of less than 95% but more than 80%, and (d) recruitment and retention: fewer than 100% but more than 80% of participants are recruited, the accrual rate is greater than 2:1 but less than 2.5, and the retention rate is less than 80% but higher than 70%.

Red: (a) intervention acceptability: a majority of stakeholders, including families raise concerns about the acceptability of the intervention, including confusion about how the intervention is sufficiently different from standard MST, (b) candidate outcome measures: fewer than 80% of recruited participants complete the outcome measures on all occasions and rates of missing data are more 10%, (c) fidelity checklist: an adapted fidelity checklist is judged to be acceptable by stakeholders with a completion rate of less than 80%, and (d) recruitment and retention: fewer than 80% of participants are recruited, the accrual rate is greater than 2:5, and the retention rate is less than 70%.

Where any of our criteria are judged to be amber or red, the study team will examine the likely causes and consider whether a mitigation strategy could be successfully implemented.

Where any of our criteria are judged to be amber or red, the study team will examine the likely causes and consider whether a mitigation strategy could be implemented.

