### Sampling

For phase 1 of this study, we worked collaboratively with the delivery team and their partner organizations to identify and invite potential participants to take part in our interviews. Phase 2: In order to maximize the probability of successful recruitment, we have adopted a multi-agency approach to recruitment and invite referrals from social services, youth offending teams, child and adolescent mental health services, and education. Fifty children and teenagers from one of three geographical regions in England (i.e., Birmingham and Sandwell, Nottingham, Yorkshire) who have met the eligibility criteria for the study, along with their families, will be invited to take part. As this is a feasibility study, and the purpose is to provide estimates of key parameters for a future pilot trial rather than to power the current study to detect statistically significant differences, a formal a priori power calculation has not been conducted [18]. However, recruiting 50 participants will provide a certain level of precision around a 95% confidence interval regarding the estimate of within-group effect. For example, the 95% confidence interval associated with a sample size of 50 is ± 13.8. We therefore believe that this sample size will provide reasonable precision around our estimates of parameters which will be used to inform the design and decision to proceed to a pilot trial including an estimate of the standard deviation of the outcome measures. We will also recruit 48 participants to take part in our interviews about the interventions which will contribute to the decision as to whether to proceed to a definitive trial. However, should a decision be made to proceed to a trial within a future study, it would be appropriate to recruit a larger sample than what we have proposed for inclusion within this feasibility study in order to model the parameters (e.g., randomization) necessary to inform the decision to proceed to a phase III trial.

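### The progression criteria give no colour to mixed results, boundary values or an unacceptable checklist, state the accrual limits inconsistently, and attach no consequence to red that differs from amber

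*Protocol article*

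**What the plan says.** The Research questions section makes the feasibility of a pilot trial the primary question. The Progression criteria section is the only place where the article turns results into a rating. It has four criteria, each with three colours.

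- **(b) outcome measures.** Green: "95% of recruited participants complete the outcome measures on all occasions and rates of missing data are below 5" per cent. Amber: "fewer than 95% but more than 80% of recruited participants complete the outcome measures on all occasions", joined by *and* to "rates of missing data are more than 5% but less than 10" per cent. Red: "fewer than 80% of recruited participants complete the outcome measures on all occasions and rates of missing data are more 10" per cent.
- **(c) fidelity checklist.** Red: "an adapted fidelity checklist is judged to be acceptable by stakeholders with a completion rate of less than 80" per cent. Green and amber carry the same acceptability condition, with completion of 95% and of 80% to 95%.
- **(d) recruitment and retention.** Green: full recruitment, accrual 2:1, retention of at least 80%. Amber: "fewer than 100% but more than 80% of participants are recruited, the accrual rate is greater than 2:1 but less than 2.5", and retention between 70% and 80%. Red: recruitment below 80%, accrual above 2:5, and retention below 70%.
- **Action.** "Where any of our criteria are judged to be amber or red, the study team will examine the likely causes and consider whether" mitigation is workable. This sentence is printed twice with almost the same wording and covers both colours. No colour is tied to proceeding or to not proceeding.

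The Study objectives and Analysis sections treat the adapted checklist as optional. The Conclusions of the abstract say that the results inform a judgement on whether progressing is advisable.

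**The concern.** A traffic-light rule is useful only if each foreseeable result gets a colour and each colour has its own meaning. Here the components within (b) and (d) are joined by *and* at every level, and no rule says what happens when they disagree. The action sentence covers only criteria judged amber or red, so a criterion without a colour escapes it, even when one component has clearly failed. Where the rule is silent, the rating behind the answer to the primary question would be settled after the results are seen. The article prints these criteria in full, so this is not detail left to another document.

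**Working it through.** No figure in the article quantifies the progression rule. Its one precision statement, "the 95% confidence interval associated with a sample size of 50 is ± 13.8", is reproduced by 1.96 × √(0.25/50) = 0.1386, or 13.86 percentage points at a proportion of 50%. Nothing below depends on it.

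**1. Criterion (d) at full recruitment.** Take 50/50 recruited.
- Green needs retention of at least 80%.
- Amber needs recruitment below 100%, which is not met.
- Red needs recruitment below 80%, which is not met.

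So at 75% retention, or at 40%, (d) has no colour and the review is not triggered. This needs no assumption about probabilities.

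**2. Criterion (b).** Assume that missing data are counted as whole forms over four assessments (baseline, mid-point, end of treatment, follow-up); the article does not define the rate. If 35 of 50 complete every occasion and 15 miss only the last form:
- completion = 35/50 = 70%, red level;
- missing = 15/(50 × 4) = 15/200 = 7.5%, amber level.

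The result has no colour. The two measures diverge by construction: one missed form removes a participant from the all-occasions count but adds only 1/200 to missing data. Two assumed patterns show the range:

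| Pattern | Input | Complete on all occasions | Forms missing | Colour |
|---|---|---|---|---|
| Independent | 98% per occasion | 0.98⁴ = 92% (amber) | 2% (green) | none |
| Independent | 94.8% per occasion | 0.948⁴ = 81% (amber) | 5.2% (amber) | amber |
| Independent | 92% per occasion | 0.92⁴ = 72% (red) | 8% (amber) | none |
| Drop-out just after baseline | 90% complete | 90% (amber) | 0.75 × 10% = 7.5% (amber) | amber |
| Drop-out just after baseline | 84% complete | 84% (amber) | 0.75 × 16% = 12% (red) | none |

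**3. Combinations of bands.**
- (b): 3² = 9, of which 3 have a colour.
- (c): acceptable or not × 3 completion bands = 6, of which 3 have a colour.
- (d): 3³ = 27, of which 3 have a colour if the red accrual limit is read as 2.5. If 2:5 is taken literally, every accrual band exceeds it, so red recruitment with red retention is red at all three accrual levels: 3 red + 1 green + 1 amber = 5 of 27.
- (a) has no joined components and is not affected.

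These are counts of combinations, not probabilities.

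**4. Boundary values.** With strict inequalities on both sides, these attainable values have no band: 40/50 = 80% (recruitment or completion), 35/50 = 70% (retention), 10/200 = 5% and 20/200 = 10% (missing forms). Checklist completion of exactly 80% has the same gap.

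**5. Accrual.** The limits are 2:1 = 2.0 (green), 2.5 (amber ceiling) and 2:5 = 2/5 = 0.4 (red floor). Since 2.0 > 0.4, the green value also meets the red condition. A ratio below 2:1 is not placed in green or amber.

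**6. Red (c).** All three colours require acceptability, so a checklist judged unacceptable has no colour. There is also no rating for the case where no adapted checklist is used.

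**The case against.** The strongest reply is that the team will colour each component separately. Each has its own three bands, and the Analysis section reports recruitment, retention, completion and missing-data rates individually. That is a natural reading, but the text does not state it: colours are defined per criterion and there is no rule for combining components. Even on that reading, the boundary gaps, the accrual limits, the unrated unacceptable checklist and the shared action remain.

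A second reply is that discretion is legitimate in a descriptive, single-group feasibility study. That stands. A reader might infer from the shared action that no result can stop progression. The article does not support this: the team may conclude that mitigation is unworkable, and the results only inform whether progressing is advisable. What is missing is a stated stop, or any stated difference between red and amber.

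A reader might also infer from the counts that most actual results will have no colour. That is not shown. Completion and missing data are linked, and recruitment and accrual plausibly are too, so the combinations are not equally likely. An assumed simulation left (b) without a colour in anything from under 1% of runs (heavy loss) to 58% (light loss). It left (d) without one in 87% to 98%, but with recruitment and accrual varied independently.

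Finally, the Discussion places the study in its last month of accrual, so rewriting recruitment and accrual limits now is partly rule-setting after the data. That also stands and limits what a revision can claim.

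**Conclusion.** The concern holds as a defect of the rule as written. Three parts follow from the text alone: with 50/50 recruited, (d) cannot be rated at any retention below 80%; an unacceptable checklist cannot be rated; and red carries no consequence distinct from amber. The boundary gaps and the conflicting accrual limits are equally plain. The 7.5% example and the patterns for (b) rest on the assumption of form-level missingness over four assessments. How often a real result would go unrated cannot be determined from the article.

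**What to change.** Reword the Progression criteria section.

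- Rate each component separately and let the worst component set the colour of its criterion. On the counts above, (b) goes from 3/9 to 9/9 and (d) from 3/27 to 27/27.
- Close every band: completion and checklist completion at least 95% / 80% to <95% / <80%; missing data <5% / 5% to 10% / >10%; recruitment 100% / 80% to <100% / <80%; retention at least 80% / 70% to <80% / <70%. Define the missing-data rate.
- Write the accrual limits in one form, say what the ratio compares, and cover all values, including those below 2:1 and exactly at each limit. The sponsor must confirm the intended red limit.
- Red (c): checklist judged not acceptable, or completion below 80%. Mark (c) not applicable if no adapted checklist is used. This takes (c) from 3/6 to 6/6.
- Give red its own consequence, for example no progression unless a documented design change addresses the cause. An automatic stop is not advised. If retention means reaching final follow-up (an assumption), those completing all occasions cannot outnumber those retained. Amber retention would then force red completion, and retention of 80% to 94% could never accompany green completion. Check that these two sets of bands are compatible before fixing them.

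Follow-up runs to April 2023, so the retention and completion rules can be settled before those data are complete. The revision should note that recruitment and accrual were already largely known. The cost is one section of rewording and a stricter rule, in which a single poor component sets the colour.

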### Exclusion criteria

Our exclusion criteria for pilot participants are as follows:

The family refuses to take part in the study.The young person lives independently, or a primary caregiver cannot be identified.The child is presenting with symptoms consistent with a psychotic illness.The child is at high risk of suicide as assessed by the clinical team assessing the referral.There is documented evidence of the child having a Full-Scale IQ < 65.There is evidence to indicate that a family member who is living with the child has been sexually abusing them and there continues to be an active and enduring risk,The child has previously received a diagnosis of an autism spectrum disorder and problematic behaviors as defined within the inclusion criteria have been judged to be associated with having a developmental disability (e.g., self-harm associated with hypersensitivity) by the clinical team assessing the referral.

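### The red accrual limit is printed as 2:5 (0.4), so every green or amber accrual ratio also meets the red accrual element; the amber band implies that 2.5:1 was meant

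*Protocol article*

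**What the plan says.** Item (d) of the Progression criteria combines recruitment, accrual and retention at each colour. The figures at the end of the first three quotes are percentages.

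- Green: "100% of participants are recruited, the accrual rate is 2:1, and the retention rate is at least 80".
- Amber: "the accrual rate is greater than 2:1 but less than 2.5, and the retention rate is less than 80% but higher than 70", with recruitment between 80% and 100% of target.
- Red: "fewer than 80% of participants are recruited", joined to "the accrual rate is greater than 2:5, and the retention rate is less than 70".

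The Analysis section lists "the accrual and retention rate and willingness of teams to recruit participants" among the outcomes used to judge feasibility. Neither that section nor the Progression criteria says what is divided by what. The Inclusion criteria require parental consent, and the Exclusion criteria include "The family refuses to take part in the study". If any criterion is amber or red, the team looks into the reasons and considers whether the problem can be mitigated.

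**The concern.** A traffic-light scale works only if each result falls in one band. From green to amber the accrual ratio gets worse as it rises, and amber stops at 2.5. The red limit should continue from there, but the printed figure lies below both other bands.

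Feasibility is the primary research question, and accrual is one of the quantities used to judge it. The Background describes engaging these families as a major difficulty. If the threshold cannot be applied as printed, someone must decide what it meant, possibly with the accrual data in view. Because the ratio's terms are not named, there would be room for choice there too.

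**Working it through.** **Inputs**, all from item (d) of the Progression criteria: green 2:1 = 2/1 = 2.0; amber above 2.0 and below 2.5; red, as printed, above 2:5 = 2/5 = 0.4.

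**Step 1: the bands as printed.** Since 2.0 > 0.4, the green value meets the red accrual element, and so does the whole amber band. The table applies three versions of the accrual rule alone.

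| Accrual ratio | As printed | Only red changed to >2.5 | Bands fully restated |
|---|---|---|---|
| 1.5 | red | no colour | green |
| 2.0 | green and red | green | green |
| 2.2 | amber and red | amber | amber |
| 2.49 | amber and red | amber | amber |
| 2.5 | red | no colour | amber |
| 2.6 | red | red | red |
| 3.0 | red | red | red |

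Changing only the red figure removes the overlap. It leaves ratios below 2.0, and exactly 2.5, without a colour.

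**Step 2: other readings of 2:5.**

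- *Recruited families first.* Green would become 1:2 = 0.5 and the red limit 2:5 = 0.4. Because red is worded as greater than the limit, 0.5 would be red and better accrual would count as worse.
- *2:5 correct and the amber ceiling wrong.* Amber would then need a ratio above 2.0 and below 0.4, which is impossible.
- *A colon printed for a decimal point (2.5), or the terms reversed (5:2 = 2.5).* Both give 2.5, which meets the amber ceiling.

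Only a limit of 2.5 makes the three bands coherent.

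**Step 3: effect on item (d) as a whole.** Red joins its three parts with *and*. Red recruitment means fewer than 0.80 × 50 = 40 families. A study at 2:1 with all 50 recruited and 80% retained is therefore not red on (d), despite the misprint. If the first term of the ratio includes the recruited families, the ratio is at least 1.0 and always exceeds 0.4. The red accrual part is then always met and adds nothing to the other two.

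**Step 4: why the terms need naming.** Suppose 50 families are recruited and R otherwise eligible families refuse.

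- Refusers kept in the first term: (50 + R)/50. For R = 25, 50, 75 and 100 this is 1.5, 2.0, 2.5 and 3.0.
- Refusers classed as excluded, with the ratio taken as eligible to recruited: 50/50 = 1.0 for every R.
- Ratio taken as referred, screened or approached to recruited: refusers stay in the count and the exclusion criterion changes nothing.

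The same refusals can thus give any colour or none, depending on a definition that the article does not state.

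**The case against.** The strongest reply is that this is one wrong punctuation mark, with the intended value printed in the amber text just above. A sensible reader would apply 2.5:1, and would read green 2:1 as a limit with anything better also green. No automatic stop depends on the figure. A condensed article may also leave the definition of accrual to the full protocol. Much of this stands, and it limits the severity. It does not remove the point: the figure is a published decision threshold, it contradicts its neighbours, and the right value has to be inferred.

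Some stronger conclusions that a reader might draw are not supported:

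- *A study at 2:1 would be judged red.* It would not, unless recruitment and retention were also red.
- *Every plausible result is misclassified.* Ratios above 2.5 are red both as printed and as evidently intended.
- *Listing refusal as an exclusion does distort the ratio.* This follows only if the first term is families meeting all the eligibility criteria. Nothing in the article links those criteria to the accrual ratio.
- *An engagement problem would go unseen.* Recruitment against target and retention are assessed separately in item (d), and the Analysis section reports both overall and by site.
- *Only 50 families will be approached, giving 25 recruits at 2:1.* Sampling does say that fifty children "who have met the eligibility criteria for the study, along with their families, will be invited to take part", but this is loose wording. The same section speaks of recruiting 50, as do the eligibility text and, in terms of families treated, the Study objectives and Design sections.

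**Conclusion.** The red accrual limit is wrong as printed. At 0.4 it takes in the green value of 2.0 and the whole amber band from 2.0 to 2.5, and no literal reading makes the bands consistent. That 2.5:1 was intended is an inference, but a strong one, because it alone continues from the amber ceiling. This rests on reading the ratio as first term over second with larger values worse, as the step from green to amber requires.

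The consequence is limited to the accrual element of item (d), and amber and red lead to the same review. The undefined ratio is a secondary point: refusal as an exclusion matters under one possible definition and not under others. Severity is minor to moderate.

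**What to change.** Restate the accrual element as green at or below 2.0:1, amber above 2.0:1 up to and including 2.5:1, and red above 2.5:1. Ratios below 2:1 and exactly 2.5:1 then also have a colour.

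Name both terms at the same time. One workable definition is families invited who meet every criterion other than consent or refusal, divided by families recruited. Say that refusers remain in the first term, and report refusals separately from ineligibility. This needs no change to the eligibility criteria.

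Record the date of the correction and whether it came before or after anyone reviewed the accrual data. The Discussion places the study in its last month of accrual, so that order matters.

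The cost is a change of wording to one element and one definition. The definition also needs counts of invited and refusing families. The article does not say whether these are kept, so the sites should confirm that they are.
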